### Sample size calculation

In our retrospective analysis, we found an 18% reduction in mortality when patients were treated with high-dose LMWH (23% mortality in the low-dose LMWH group versus 5% mortality in the high-dose LMWH group, OR 0.19, 95% CI: 0.07 to 0.55).^25^ Although this is a substantial reduction, it was derived from a retrospective, non-randomised design, which limits the ability to assess causal inference and make proper adjustments for confounding prognostic variables. Since we cannot assume this effect size to be accurate without further validation, we aim to conduct a phase II RCT with a total of 100 patients (50 patients per group). After the inclusion and follow-up of these patients, we hope to perform a more reliable power calculation to proceed to a phase III trial.^31^ Besides clinical data, this study will help evaluate the financial and logistical feasibility (including compliance to the study medication, data collection and costs) of establishing a full-scale study.

Each year, 120–125 patients with aSAH are admitted to the Amsterdam UMC, with 80–90 of these patients receiving coiling of the causative aneurysm. Considering the exclusion criteria, we estimate that roughly 25–50 patients per year could be eligible for the ISCHEMIA trial.

### Statistical analysis

All enrolled patients will be evaluated for the primary and secondary outcomes using an intention-to-treat analysis. To ensure the robustness of the findings, a per-protocol and as-treated analysis will also be conducted, excluding participants who do not complete follow-up, switched treatment groups, had major protocol violations and/or non-adherent patients. Baseline characteristics will be summarised by means of simple descriptive statistics. Continuous data with a parametric distribution will be presented as mean and SD, while non-parametric data will be presented as median and IQR. For between-group comparisons, independent samples t-tests or Mann-Whitney U tests will be used as appropriate. Categorical data will be presented as percentages, with the χ² test used for between-group comparisons.

The treatment effect on the primary outcome (30-day mortality) will be analysed using multivariable logistic regression, adjusting for any clinically relevant baseline imbalances if necessary. Secondary outcomes will be analysed using independent samples t-tests, Mann-Whitney U tests, χ² tests and multivariable linear and logistic regression models, as appropriate. Sensitivity analyses will also be performed, allowing early withdrawal of life support to be considered as a potential confounding variable.

All statistical uncertainty will be expressed using 95% CIs. Statistical analyses will be performed using SPSS (IBM, Armonk, New York, USA), with a significance level set at p<0.05, and all tests will be two-sided.

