**Methods and analysis:**

This is a single-centre, prospective, phase II randomised controlled trial. From January 2022, all eligible patients will be recruited. 100 patients will be randomised to the intervention arm, that is, nadroparin two times per day 5700 AxaIU, or the control arm, that is, nadroparin once daily 2850 AxaIU in patients with body weight ≤100 kg or once daily 5700 AxaIU in patients with body weight >100 kg, both for up to 21 days. The trial includes a 6-month follow-up period. The primary objective is 30-day mortality rate. Secondary outcomes include assessment of DCI, complications during admission, discharge location, clinical outcome (modified Rankin Scale), quality of life and total healthcare costs at 3 and 6 months follow-up.

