Patients with anticoagulants receive reversal agents on admission as standard care. In the case of vitamin K antagonists and heparin derivatives, patients in the intervention group will only start with high-dose LMWH after receiving reversal agents, with an international normalised ratio ≤1.5, and 24 hours after the initial bleeding (unless a craniotomy is indicated). In the case of direct oral anticoagulants (DOACs) use, high-dose LMWH will not be administered until 48 hours after receiving the last dose of DOAC since there are often limited options to reverse its action. Antiplatelets are often not counteracted unless a craniotomy is performed. In the case of antiplatelet use, high-dose LMWH will be postponed until 24 hours after the initial bleeding. In the case of dual antiplatelet therapy, a cardiologist will be consulted to assess whether it’s possible to switch to high-dose LMWH. If this is not possible, the patient will be excluded. The investigator or treating physician can decide to withdraw a subject from the study for urgent medical reasons. If it is revealed after inclusion that one of the exclusion criteria was present in a certain patient on admission, this patient will remain included in the study and this is recorded as a protocol violation. Depending on the criterion, actions are undertaken. For instance, nadroparin can be stopped (history of heparin-induced thrombocytopenia, history of hypertensive or diabetic retinopathy, endocarditis) or switched to an alternative type of LMWH or the higher dose will be switched for a prophylactic dose (severe renal impairment, intestinal tract bleeding). If nadroparin is not available or not tolerated, mostly due to skin reactions, other LMWHs can be administered depending on local availability and according to the doses listed in online supplemental appendix A. In case of mild renal failure (creatinine ≥30 mL/min and <50 mL/min), the dose of LMWH in the intervention arm will be reduced by 25%. Emergency surgical procedures (eg, lumbar puncture, insertion of ventricular catheter or lumbar drain) and procedures for bleeding in patients receiving a higher dose of LMWH conform to standard routine clinical care. A flowchart is included in online supplemental appendix B.

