### Outcomes

The primary objective is to evaluate whether treatment with high-dose LMWH in patients with coiled aSAH significantly reduces mortality assessed at 30 days after the initial bleeding. Secondary objectives are to evaluate whether this treatment significantly reduces the presence and severity of DCI (measured by the Modified National Institutes of Health Stroke Scale),^29^ increases the incidence of major bleeding (defined as a fatal bleeding and/or symptomatic bleeding in critical areas or organs (such as intracranial, intraspinal, intraocular, retroperitoneal, intra-articular, pericardial or intramuscular bleeding causing compartment syndrome) and/or bleeding resulting in a haemoglobin drop of 1.2 mmol/L or more, or requiring a transfusion of two or more units of whole blood or red cells) and non-major bleeding (defined as all reported bleedings not classified as major),^30^ increases the risk of haemorrhagic complications after shunt placement or lumbar puncture, reduces other SAH-related complications (such as severe hyponatraemia, postprocedural aneurysm rupture, rebleeding, delirium, epilepsy, diffuse parenchymal swelling or nosocomial infections), reduces the incidence of shunt-dependent hydrocephalus, increases the rate of discharge to home, improves quality of life at 6 months, enhances cognitive functioning at 6 months, increases the likelihood of a favourable outcome at 6 months and reduces mortality at 6 months. Outcome assessments are done by a trial nurse at the outpatient clinic 6 months after the initial bleeding, with the standard follow-up performed on the same day. The trial nurse is blinded for group allocation and does not participate in the medical treatment of the included patients. In addition, peak anti-Xa levels are measured at 12:00 on day 7 following the ictus and are readily available for analysis. A comprehensive panel of coagulation and inflammatory biomarkers is also being collected and will be analysed after completion of patient inclusion. The biomarkers include von Willebrand factor, syndecan-1, soluble thrombomodulin, tumour necrosis factor-alpha, interleukin (IL)-6, IL-8, soluble vascular cell adhesion molecule-1, angiopoietin, a disintegrin and metalloproteinase with thrombospondin motifs 13, D-dimer and coagulation factor III (also known as tissue factor). All biomarker measurements are performed on day 7 following the ictus.

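### One exclusion list for both the per-protocol and as-treated analyses makes the second a copy of the first and lets both select on events after randomisation

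*Protocol article*

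**What the plan says.** All points are from the protocol article.

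- **Main analysis (Statistical analysis).** "All enrolled patients will be evaluated for the primary and secondary outcomes using an intention-to-treat analysis".
- **Additional analyses (same section).** "To ensure the robustness of the findings, a per-protocol and as-treated analysis will also be conducted", followed directly by one list of exclusions that grammatically governs both: "excluding participants who do not complete follow-up, switched treatment groups, had major protocol violations and/or non-adherent patients".
- **Primary endpoint (Outcomes).** The aim is to show that treatment "significantly reduces mortality assessed at 30 days after the initial bleeding".
- **Follow-up (Abstract, Methods and analysis).** "The trial includes a 6-month follow-up period". The Outcomes section places the blinded assessment at an outpatient visit 6 months after the bleed.
- **Dose changes (Interventions).** Among the actions for a patient found after inclusion to have met an exclusion criterion on admission, "the higher dose will be switched for a prophylactic dose (severe renal impairment, intestinal tract bleeding"; such a patient stays in the trial and is recorded as a protocol violation. Separately, in mild renal failure the dose is reduced by 25% in the intervention arm.
- **Interruptions (Discussion, limitations).** Some patients are expected to miss doses because emergency procedures require a temporary stop.
- **Progression threshold (Discussion).** A 5% absolute or at least 20% relative reduction in mortality would justify a larger trial. No analysis set is named.

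**The concern.** There are two separate problems.

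The first is one of definition. An as-treated analysis exists to place patients who changed treatment in the group they actually received. If they are excluded instead, it has no content of its own, and its agreement with the per-protocol result is guaranteed rather than informative.

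The second is selection. Three of the listed criteria (follow-up not completed, switching, non-adherence) are defined by what happens after randomisation, in a trial whose endpoint is early death in severely ill patients. Missed doses, dose changes and incomplete follow-up may all be related to prognosis, and some dose changes have no counterpart in the control arm. A comparison restricted in this way no longer has the protection of randomisation. It cannot serve as a robustness check, and it could mislead if the phase III decision were read from it.

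**Working it through.** The plan states no figure for this point, so there is none to reproduce.

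**Step 1. Are the two analyses different?** Apply the list. Once everyone who switched is removed, treatment received equals treatment allocated for every remaining patient. The as-treated groups are then the per-protocol groups: same patients, same arms, same estimate. This needs no assumption.

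**Step 2. What does the follow-up criterion do to deaths?** The section does not say which follow-up is meant or how a death is handled. There are two readings:
- *A death counts as a completed outcome.* The criterion removes no deaths.
- *A death before 6 months counts as not completing.* Every 30-day death leaves both arms. At the retrospective in-hospital rates quoted under Sample size calculation, that is 50 × 0.23 = 11.5 and 50 × 0.05 = 2.5, or 14 expected deaths. Mortality becomes 0% in both arms and the odds ratio cannot be estimated.

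**Step 3. Which removals can be one-sided?** The change from the higher to a prophylactic dose, and the 25% reduction, can occur only in the intervention arm. The text does not say whether either counts as switching or non-adherence. Stopping nadroparin, temporary interruption and withdrawal can occur in either arm.

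**Step 4. How large could the bias be?** Suppose there is no true effect and mortality is 23% in both arms (the retrospective low-dose rate). Let *s* be the share of the high-dose arm removed and *m* the mortality among those removed, with nobody removed from the control arm. Both *s* and *m* are assumptions; the documents give neither.

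Per-protocol mortality in the high-dose arm = (0.23 − *s·m*)/(1 − *s*)

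Apparent absolute reduction = *s*(*m* − 0.23)/(1 − *s*)

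Example: *s* = 0.10, *m* = 0.40 gives (0.23 − 0.04)/0.90 = 0.211. The odds ratio is (0.211/0.789)/(0.23/0.77) = 0.90.

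| *s* | *m* | High-dose mortality | Absolute reduction (points) | Relative reduction | Odds ratio | Chance of observing a reduction ≥5 points |
|---|---|---|---|---|---|---|
| 6% | 40% | 21.9% | 1.1 | 4.7% | 0.94 | 30.4% |
| 6% | 60% | 20.6% | 2.4 | 10.3% | 0.87 | 35.9% |
| 10% | 40% | 21.1% | 1.9 | 8.2% | 0.90 | 35.5% |
| 10% | 60% | 18.9% | 4.1 | 17.9% | 0.78 | 45.1% |
| 20% | 40% | 18.75% | 4.25 | 18.5% | 0.77 | 47.8% |
| 20% | 60% | 13.75% | 9.25 | 40.2% | 0.53 | 71.4% |

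The last column is an exact binomial calculation with 50 control patients and 50(1 − *s*) high-dose patients. In the ITT set (50 per arm, no effect) the same chance is 27.6%. With *m* = 23% there is no bias, and the chance is 26.1% to 29.8% from the smaller numbers alone, so the first row barely differs from chance.

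The sign of the bias follows *m* − 0.23. If those removed die more often than average, the high dose looks better; if less often, it looks worse. On average, only the last row reaches either progression threshold.

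**The case against.** The strongest reply is that the ITT analysis covers all enrolled patients for primary and secondary outcomes, so a null or harmful result would be visible there. That stands, and it limits the severity.

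A reader might infer that these analyses delete the deaths. The documents do not support that as the stated rule: nothing says a death is incomplete follow-up. The Data safety analysis section schedules a review once 100 patients have completed 30-day follow-up, in a trial of 100, which suggests that patients who die count as complete. Deleting every death would also leave 0% in both arms and so would not favour the high dose. What remains is an ambiguity worth a clause.

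A reader might also infer that patients are removed, in one arm only, because the high dose harmed them. The change to a prophylactic dose is listed for exclusion criteria present on admission and found later, not for treatment-emergent bleeding. A control patient with the same criterion is equally a protocol violation. Only the dose action is specific to one arm. The management flowchart in the supplement is not at hand, so other dose changes cannot be judged.

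The article also says "The investigator or treating physician can decide to withdraw a subject from the study for urgent medical reasons". A reader might take this to mean that vital status is then lost. The article does not say so, and a condensed report may leave data collection after withdrawal to the full protocol.

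Finally, exact definitions of adherence and of a major violation commonly sit in the analysis plan, and their absence is no finding. The objection here is to the rule that is stated: one list, including switchers, for both analyses. The authors may have meant it for the per-protocol set alone, but the sentence does not say so.

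**Conclusion.** The point holds in limited form. As written, the as-treated analysis duplicates the per-protocol analysis, which is certain from the text alone. Both condition on post-randomisation events that can be related to death, and some of the possible removals have no control-arm counterpart, so neither can support the robustness claim made for them.

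Bias towards the high dose is possible, not established. Its size and direction depend on how many patients are removed and how they fare, and the documents give neither. The range of odds ratios in the working rests entirely on the assumed values of *s* and *m*, on removal from one arm only, and on 23% mortality in both arms. The ITT result is not affected. Severity is minor to moderate: the damage is to the supportive analyses and to any phase III decision read from them.

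**What to change.** 1. **As-treated.** Classify each switcher by the treatment actually received and exclude nobody for switching, or delete this analysis.
2. **Per-protocol, 30-day mortality.** State that death is a completed outcome. Limit the follow-up exclusion to unknown 30-day vital status. Do not count interruptions or dose changes that the protocol itself permits as switching or non-adherence.
3. **Role.** Label both analyses supportive, and state in the Discussion that the phase III threshold is judged on the ITT set.

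The cost is a few reworded sentences and a slightly less clean per-protocol set. No additional patients or data are needed, and no clinical rule changes.

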### Allocation and randomisation

After obtaining informed consent, patients will undergo randomisation with stratification for World Federation of Neurosurgical Societies (WFNS) score. Five strata were defined, one for each WFNS score. Within each stratum, separate randomisations are performed between the intervention and control group to ensure a balanced randomisation based on disease severity. This is particularly important because, in patients with high-grade WFNS scores, goals of care may shift toward comfort-focused measures, which can independently affect mortality outcomes regardless of the intervention. Stratification by WFNS grade helps mitigate this potential source of bias. Randomisation is conducted using a web-based permuted block system and performed by the principal investigator or executive researcher. This system employs permuted blocks of variable sizes, ranging from two to six patients, to minimise the predictability of group allocation and ensure balanced sample sizes in each study arm. Patients are randomised in a 1:1 ratio and assigned to one of the two treatment arms.

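### The imbalance-triggered covariate rule for 30-day mortality would practically never bring in WFNS grade, the factor the trial stratifies on

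*Protocol article*

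**What the plan says.** Under Statistical analysis, the primary model is set out in one sentence: the treatment effect on 30-day mortality will be "analysed using multivariable logistic regression, adjusting for any clinically relevant baseline imbalances if necessary". That section lists no covariates. The only other adjustment it mentions is a sensitivity analysis for early withdrawal of life support, which happens after randomisation.

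Under Allocation and randomisation, the trial stratifies by WFNS: "Five strata were defined, one for each WFNS score". Allocation is 1:1 within each stratum, using "permuted blocks of variable sizes, ranging from two to six patients". The stated aim is "to ensure a balanced randomisation based on disease severity", and the stated reason is that "in patients with high-grade WFNS scores, goals of care may shift toward comfort-focused measures, which can independently affect mortality outcomes".

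**The concern.** The two sections work against each other. The design makes WFNS balanced, while the analysis admits a covariate only when it is imbalanced. Applied as written, the rule passes over the one variable that the article gives a reason to account for, and can pick up chance differences in others.

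Two things are at stake. First, a test that ignores a prognostic stratification factor uses a standard error that takes no credit for the balance achieved, so it rejects too rarely and loses power. The trial has little power to spare, as its own Discussion concedes. Second, what counts as clinically relevant, and when adjustment is necessary, is undefined. The covariates behind the primary result would therefore be settled after the data have been seen, in a trial where treatment is open-label.

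**Working it through.** **Inputs from the article.** 50 patients per arm; five WFNS strata; permuted blocks of two to six (simulated as 2, 4 or 6 at random); two-sided 5% level; retrospective mortality 23% (low dose) and 5% (high dose). The sample size has no stated power basis, so there is no power figure to reproduce.

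**Assumptions not in the article.** WFNS I to V in proportions 35/22/8/15/20%; control mortality 23% overall; log-odds of death linear in grade, with an odds ratio (OR) per grade of 1.5, 2, 2.5 or 3. Effects tested: none, 23% vs 10%, and 23% vs 5%. There were 3,000 simulated trials in each of 12 scenarios, 36,000 in all. Simulation error is √(0.05×0.95/3000) ≈ 0.4 points near 5% and √(0.25/3000) ≈ 0.9 points near 50%.

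**Step 1: would the rule pick WFNS?** In the 36,000 trials, a chi-square test of WFNS by arm never gave p<0.20 (median p 0.99). The largest difference between arms within a grade averaged 1.4 patients, never exceeded 3, and reached 3 in about 4% of trials.

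**Step 2: why the unadjusted test is conservative.** On the risk-difference scale the unadjusted variance uses p(1−p) overall. After stratified randomisation the actual variance uses the within-grade average Σwₖpₖ(1−pₖ). At OR 2 per grade, mortality by grade is about 7/13/22/36/53%, so:

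- within-grade: 0.35×0.0651 + 0.22×0.1131 + 0.08×0.1716 + 0.15×0.2304 + 0.20×0.2491 = 0.1458
- overall: 0.231×0.769 = 0.177
- ratio of standard errors: √(0.1458/0.177) ≈ 0.906
- true rejection rate: P(|Z| > 1.96/0.906 = 2.16) ≈ 3.1%

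The same sum gives 4.2%, 2.1% and 1.5% at OR 1.5, 2.5 and 3. The simulation below agrees in direction and approximate size.

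**Step 3: rejection rates (%).** Unadjusted is a chi-square test; adjusted is a likelihood-ratio test with WFNS as one linear term; CMH is stratified by grade.

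| OR per grade | No effect: unadj / linear / CMH | 23% vs 10%: unadj / linear / CMH | 23% vs 5%: unadj / linear / CMH |
|---|---|---|---|
| 1.5 | 4.0 / 5.5 / 4.7 | 42.4 / 46.0 / 43.7 | 78.9 / 81.6 / 79.8 |
| 2 | 2.6 / 5.3 / 4.7 | 42.0 / 48.8 / 46.7 | 79.1 / 84.2 / 82.5 |
| 2.5 | 2.0 / 5.5 / 4.8 | 41.1 / 53.5 / 50.8 | 79.2 / 85.6 / 83.9 |
| 3 | 1.9 / 6.0 / 5.4 | 42.2 / 56.9 / 54.5 | 81.6 / 88.7 / 87.3 |

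With the linear term the gain runs from 81.6 − 78.9 = 2.7 to 56.9 − 42.2 = 14.7 points. A separate run over OR 1.5 to 2.5 put the smallest gain at about 2. With CMH the gain runs from 79.8 − 78.9 = 0.9 to 54.5 − 42.2 = 12.3 points.

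A like-for-like check used likelihood-ratio tests with and without WFNS, a mix of 35/20/10/15/20% and mortality by grade of 6/12/22/33/56%. It gave 2.9% vs 5.3% under no effect, and power of 34.1% vs 40.8% (23% vs 11%), 56.2% vs 63.4% (23% vs 8%) and 77.9% vs 82.1% (23% vs 5%).

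**Step 4: the odds ratio and its standard error** (OR 2 per grade, 23% vs 10%, Firth fits).

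- Mean log OR: −0.971 unadjusted, −1.131 adjusted, that is ORs of about 0.38 and 0.32.
- Mean SE of the log OR: 0.595 unadjusted, 0.644 adjusted.
- Ratio of estimate to SE: 0.971/0.595 = 1.63 against 1.131/0.644 = 1.76.

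The SE rises with adjustment, but the estimate moves further from zero by more. The shift arises because the odds ratio over all grades together differs from the one within grades.

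**Step 5: how many terms the data can carry.** Expected deaths at the retrospective rates: 50×0.23 + 50×0.05 = 14. Treatment plus four WFNS indicators is five parameters, or 14/5 = 2.8 deaths each. Treatment plus one WFNS term is two, or 14/2 = 7.

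**The case against.** The strongest reply is that the article does not exclude WFNS, and that covariate lists commonly belong in an analysis plan, which is not shown. This stands in part: that plan may name WFNS. But the article is not merely silent. It states a rule for the primary model, and that rule works through imbalance. Naming WFNS unconditionally would change the rule.

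A second reply is that this is a phase II trial which disclaims definitive conclusions, and that a conservative test adds no false positives. That is fair, and it limits the severity.

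Several stronger readings are tempting but not supported:

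- That the rule cannot select WFNS. The criterion is clinical judgement, and small differences from incomplete blocks remain possible. The article does not say that its baseline tests drive the choice.
- That WFNS is the strongest prognostic variable. The article links high grades to mortality but gives no ranking or effect size.
- That precision of the odds ratio is lost. Step 4 shows the SE of the log OR is smaller without WFNS.
- That covariates will be chosen by people who know the allocation. Treatment is open-label, but the article does not say who chooses covariates or whether the analyst is blinded.
- That the plan cannot yield the quantities in the Discussion's progression threshold (a 5% absolute or 20% relative reduction in mortality). Both follow directly from the mortality percentages by arm.

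**Conclusion.** The point holds as a badly chosen covariate rule. As written, it would practically never bring in the stratification factor, and it leaves the primary covariate set open until the data are seen.

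If WFNS is left out, the test rejects in about 2% to 4% of trials under no effect instead of 5%, the odds ratio is attenuated, and roughly 2 to 15 points of power are lost. The low end applies if WFNS is weakly prognostic or the treatment effect is very large. At the high end, part of the gain may come from the linear-term test running slightly above 5% (6.0% at OR 3 per grade). The direction does not depend on the exact assumptions, provided WFNS is prognostic; the size depends on the WFNS mix and prognostic strength, which the article does not give.

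This should be fixed, but it does not threaten the trial's validity.

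**What to change.** Before database lock, replace the imbalance trigger with a primary model fixed in advance: 30-day mortality on treatment and WFNS, whatever the observed balance. Use a sparse form, such as one ordinal or grouped WFNS term, a WFNS-stratified CMH test, or a Firth-penalised logistic model. Four separate indicators are too many for about 14 deaths. Any further covariates belong in secondary models and are named in advance.

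A useful addition is to report the WFNS-standardised risk difference and risk ratio with 95% confidence intervals beside the odds ratio, because the Discussion states its progression threshold on those scales.

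The cost is a sentence or two in the plan and, with a single ordinal term, one degree of freedom. No new data are needed, since WFNS is recorded for randomisation.
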